### 2.3 Eligibility criteria

**Inclusion criteria:** 1) Aged between 18 and 65 years; 2) Experiencing mild-to-moderate depression, anxiety, and insomnia, defined as a Patient Health Questionnaire-9 (PHQ-9) score between 5 and 19, a General Anxiety Disorder-7 (GAD-7) score between 5 and 14, or an Insomnia Severity Index (ISI) score between 8 and 21; 3) Understand and be able to follow written and oral instructions in Chinese to complete the assessment questionnaires; 4) Willing and able to provide informed consent.

**Exclusion criteria:** 1) History of alcohol and/or substance abuse disorder; 2) history of other major psychiatric or psychotic disorders (e.g., mania, schizophrenia, bipolar disorder, post-traumatic stress disorder or obsessive-compulsive disorder); 3) History of major neurologic disorder (e.g., Parkinson disease, Alzheimer disease or other dementia, brain tumor, seizure disorder or delirium episode); 4) Current active suicidal or self-injurious potential necessitating immediate treatment, or score ≥1 on the 9th item (suicidal ideation) in PHQ-9; 5) History of serious chronic illness, such as cancer, stroke, heart diseases, end-stage liver and kidney diseases; 6) Pregnant or lactating women; 7) Currently undergoing prescribed psychotropic medication, psychotherapy or TCM treatments for sleep and mood disturbances; 8) Allergic to CHM; and 9) Concurrent participation in other clinical trials.

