**Figure 2. f2:**
[figure not shown]
Stepped-care intervention. Note: Mild symptoms: a PHQ-9 score ranging from 5 to 9, a GAD-7 score from 5 to 9, or an ISI score from 8 to 14; Moderate symptoms: a PHQ-9 score ranging from 10 to 19, a GAD-7 score from 10 to 14, or an ISI score from 15 to 21; Severe symptoms: a PHQ-9 score ranging from 20 to 27, a GAD-7 score from 15 to 21, or an ISI score from 22 to 28.

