### 2.9 Recruitment

We will approach potential participants in the community via interactive face-to-face campaigns, public activities (e.g., interactive workshops/campaigns) across the territory, and advertisements in local newspapers and social media. Interested individuals will be invited to complete an online assessment to confirm eligibility.

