### 2.13 Data collection

Following the provision of informed consent during the first visit to the clinic, all participants will complete a validated questionnaire as a baseline assessment. This will be followed by a structured interview to collect basic demographics of each participant, including date of birth, gender, education, employment status, income, household size, and personal habits such as caffeine intake, alcohol consumption, smoking, and exercise routines. Additionally, medical history and any concurrent treatments will be documented. Afterward, participants will undergo a TCM body constitution assessment, during which a Chinese medicine practitioner will prescribe the CHM. At different stages during the intervention period, participants will be required to complete validated questionnaires online and participate in tele-consultations for TCM body constitution assessments (see
Table 3 and
Figure 3). After completing all interventions, participants will be invited to finish a final assessment at the clinic. A follow-up assessment will take place 6 or 12 weeks after the intervention via tele-consultation. To promote participant retention and ensure complete follow-up, participants in Level 1 will be contacted bi-weekly, and those in Level 2 and 3 will be contacted weekly by phone. One day prior to the face-to-face consultation, we will send participants a message reminder of the appointment date and time. Four attempts will be made on two different days to contact each participant.

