### 2.15 Statistical methods

Data will be presented as mean (standard deviation) or frequency (percentage). The Hussey-Hughes model will be utilized for data analysis, where linear mixed models will be used for continuous outcomes, and generalized estimating equations will be used for categorical outcomes. Pairwise comparisons will be performed using linear contrast. Statistical significance will be considered at p < 0.05. The Holm procedure will be applied to address multiplicity. All statistical analyses will be performed using SAS OnDemand for Academics. All outcomes will be statistically analyzed according to the intention-to-treat principle and the per-protocol population separately.

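### The primary model named in section 2.15 carries no participant covariates in its standard form, which costs precision and leaves any measured recruitment difference uncorrected

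*Protocol article*

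**What the plan says.** **Model.** Section 2.15 commits the analysis to a named model, Hussey-Hughes, under which "linear mixed models will be used for continuous outcomes". The section goes on to linear contrasts, the Holm procedure and two analysis populations. It lists no participant covariates and rules none out.

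**Covariates available.** Section 2.13 provides that "all participants will complete a validated questionnaire as a baseline assessment", followed by a "structured interview to collect basic demographics of each participant", "including date of birth, gender, education, employment status, income, household size" among them. Table 3 places PHQ-9, GAD-7 and ISI at each level's baseline (A_bs), immediately after the intervention and at follow-up.

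**Screening.** Under section 2.9, "Interested individuals will be invited to complete an online assessment to confirm eligibility". Section 2.3 defines eligibility by the three scales, for example a "Patient Health Questionnaire-9 (PHQ-9) score between 5 and 19". The three ranges are alternatives, joined by *or*. The note to Figure 2 splits them into mild and moderate bands.

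**Order of events.** Under section 2.10 the districts are randomised 4 weeks before the study begins. Section 2.11 keeps the list from the screeners who enrol participants. Section 2.12 says participants cannot be blinded.

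**The concern.** The primary scales should vary widely between people before anyone is treated. Eligibility runs from mild to moderate and needs only one scale in range, so someone admitted on insomnia alone may score minimal on PHQ-9 or GAD-7. A model with period, exposure and district terms puts all of that variation into the residual, although part of it could be predicted from information obtained before treatment.

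District randomisation also fixes only the order in which districts start. It does not decide who volunteers in each period. If the people who come forward in exposed periods differ from those in unexposed periods, the unadjusted model attributes that difference to the intervention, even where it is measured.

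Two things are therefore at stake: precision on all three primary scales, and the ability to correct for measured differences in recruitment.

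**Working it through.** **The plan's own figure (section 2.8).** Design effect 1 + (65 - 1) x 0.01 = 1.64. Then 260 x 1.64 = 426.4, which the article takes as 428, and 428 / 0.7 = 611.4, giving 612. The chain from 260 reproduces and uses no covariate adjustment. How 260 itself was obtained is a separate matter and does not affect this point.

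**Inputs for the precision check**
- From the article: 18 districts; 4 steps after an initial unexposed period, so 5 periods; ICC 0.01; 428 participants after attrition; target effect d = 0.2.
- Assumed: districts split 4/4/5/5 over the steps (within the stated 4-6); one observation per person, spread evenly, so 428 / 90 = 4.76 per district-period; covariates correlating 0.3 to 0.6 with the outcome, so R2 = 0.09 to 0.36. The article gives no R2.

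**Formula.** With total variance 1, the district variance is t = 0.01 and the variance of a cell mean is s = 0.99 x (1 - R2) / 4.76. The Hussey-Hughes variance of the effect is

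I s (s + T t) / [(I U - W) s + (U^2 + I T U - T W - I V) t]

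Here I = 18 and T = 5. For this layout U = 43 (exposed cells), W = 573 (sum of squared exposed-district counts by period) and V = 125 (sum of squared exposed-period counts by district). Then I U - W = 774 - 573 = 201, and U^2 + I T U - T W - I V = 1849 + 3870 - 2865 - 2250 = 604.

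| R2 | s | Variance | SE (SD units) | Fall in SE |
|---|---|---|---|---|
| 0 | 0.208 | 0.967 / 47.88 = 0.0202 | 0.142 | - |
| 0.09 | 0.189 | 0.816 / 44.12 = 0.0185 | 0.136 | 4% |
| 0.36 | 0.133 | 0.439 / 32.82 = 0.0134 | 0.116 | 19% |

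Power at d = 0.2 under this layout, as the normal probability below 0.2 / SE - 1.96, moves from 0.29 to 0.31 and 0.41. These values compare adjusted with unadjusted analysis under the one-observation assumption. They do not restate the trial's power.

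**Does leaving covariates out bias the estimate?** In 20,000 simulated trials with a true effect of 0.20 and R2 = 0.3, the unadjusted mean was 0.201 (SD 0.142) and the adjusted mean 0.200 (SD 0.120). There is no bias. The loss is in spread only.

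**What if recruits differ systematically?** The shift equals the severity difference between exposed and unexposed recruits times the slope of outcome on severity. An assumed difference of 0.1-0.3 SD and an assumed slope of 0.3-0.7 give 0.1 x 0.3 = 0.03 SD up to 0.3 x 0.7 = 0.21 SD, or 15% to 105% of d = 0.2. The article supplies neither input.

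**The case against.** The strongest reply is that section 2.15 is one condensed paragraph of a journal article. Linear mixed models can carry covariates, the text does not say that the analysis is unadjusted, and covariate lists are commonly left to an analysis plan, which is not shown here. This stands in part: the article contains no false statement on this point, and silence alone would be no finding. However, the article names a specific model whose standard form has no participant terms, so a reader who takes that name at its word will fit it without them.

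Three further objections hold.
- A reader might infer that the severity spread or chance imbalance distorts the treatment estimate. The simulation shows that it does not; both are reflected in the standard error.
- A reader might infer that recruitment was in fact unbalanced. Nothing in the article shows this, the same eligibility limits apply throughout, and screeners do not see the list. Unblinded enrolment after randomisation makes an imbalance possible and no more.
- A reader might divide 612 by 90 cells, get 6.8 people per cell, and conclude that the mix in each cell is very unstable. That places each person in one cell only, whereas Table 3 measures each person repeatedly. Within-person comparisons already remove stable differences.

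The remedy also has a limit. The article does not say that screening scores were kept, and Table 3 has no screening column.

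**Conclusion.** The point holds as a modest, conditional improvement to a stated method. Without participant covariates the estimate remains unbiased under the randomisation, but it is less precise than the available information allows. Adjustment would cut the standard error by about 4-19%, given an assumed R2 of 0.09-0.36 and one observation per person. The gain is smaller if a participant random effect is fitted, and may fall short of this range if only age and sex can be used.

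The same assumptions could be expressed as 1 / (1 - R2) = 1.10 to 1.56, that is, as worth 10-56% more participants. That should not be taken as the expected saving: it ignores the district variance, which adjustment does not reduce here, and it does not apply once a participant effect is in the model.

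The second consequence is protective. If recruitment differs between exposed and unexposed periods, the unadjusted model cannot correct even the measured part. The 0.03-0.21 SD shift shows what could happen under assumed inputs and is not an estimate for this trial.

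The ranges in section 2.3 should not be read as the entry distribution of each scale, because qualifying on one scale is enough.

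**What to change.** State in section 2.15, or in the analysis plan, before any analysis:
- The primary linear mixed model for each of PHQ-9, GAD-7 and ISI includes age and sex as fixed covariates.
- That scale's own eligibility-screening score is added as a fixed covariate if it was retained.
- The A_bs score is not used as a covariate where it is also an analysed unexposed outcome.
- The unadjusted Hussey-Hughes estimate is reported alongside.

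Timing matters: the article says recruitment is complete and expects data collection to end in July 2025, and covariates chosen after results are seen would carry little weight.

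The cost is two degrees of freedom per scale, or three with the screening score, plus a check that the screening scores were kept. No new data collection is needed. If the scores were not kept, adjust for age and sex alone and say so.

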## 2. Methods

### 2.1 Trial design

This interventional study will be a multicenter, pragmatic, stepped-wedge, cluster randomized trial. Randomization will be carried out based on the 18 geographic districts in Hong Kong. The CHM intervention will be sequentially implemented in 4-6 districts per step according to a computer-generated random number while the remaining clusters will continue to stay unexposed to the intervention. After a 4-step exposure, all districts will receive the CHM intervention (
Figure 1). The study was approved by the Hong Kong Baptist University Research Ethics Committee (Approval No.: REC/22-23/0709) on April 8, 2024, and prospectively registered with the Chinese Clinical Trial Registry (ChiCTR2400083685) on April 30, 2024,
https://www.chictr.org.cn/hvshowprojectEN.html?id=251238&v=1.0. Recruitment started on May 1, 2024, and has already been completed. Data collection is expected to end in July 2025. The study is conducted according to the guidelines for good clinical practice (ICH/GCP) and the Declaration of Helsinki.
^
40
^ This protocol strictly adhered to the Standard Protocol Items: Recommendations for Interventional Trials (SPIRIT) 2013 statement (
**refer to data availability**).

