### 2.8 Sample size

We first estimated the sample size using the approach routinely employed in the standard randomized controlled superiority trial setting. Estimation of sample size was performed using G*Power 3.1.
^
49
^ Since there has been no study to evaluate the effectiveness of a stepped-care CHM intervention in patients with mild-to-moderate depression, anxiety, and insomnia, we conservatively estimated the effect size (Cohen’s d) of the intervention on the primary outcome is of small magnitude ~ 0.2.
^
50
^ Given the two-sided α of 0.05, power of 0.95, the sample size for a standard superiority RCT will be 260. Given the stepped wedge design of the present cluster randomized trial, we multiply the sample size by design effect which equals to 1+(m-1) x ICC, where m is the average cluster size and ICC is the intra-cluster correlation coefficient.
^
51
^ With reference to previous literature, the ICC equals to 0.01.
^
52
^ We operationalize the 18 districts in Hong Kong into 4 clusters, therefore the average cluster size m will be 260/4 clusters = 65. Thus, the design effect will be 1+(65-1) x 0.01 = 1.64. Therefore, the total sample size will be 260 x 1.64 = 428 (rounded up from 426.4). Considering the possibility of participant attrition during the 24-week study period, we have intentionally adopted a significant drop-out rate of 30% during the sample size calculation. This decision was made to ensure adequate statistical power.
^
53
^ As a result, the final sample size was determined to be 612 (428/0.7) participants.

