### 2.10 Sequence generation

Randomization of the sequence of initiation in 18 districts will be conducted 4 weeks prior to the commencement of study by an independent researcher (IR) not involved in assessment or delivery of the intervention. All 18 districts will receive no interventions in the first 4 weeks. After the first 4 weeks, 4-6 districts will initiate the stepped-care CMH intervention and this procedure continues at 4-week intervals, until all 18 districts cross over to the intervention phase.

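### GEE tests of categorical outcomes rest on only 18 randomised districts; run in its ordinary form, the test would reject about 8-12% of the time at a nominal 5%, so section 2.15 should fix the clusters and a small-sample correction

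*Protocol article*

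**What the plan says.** Section 2.15 divides the analysis by type of outcome: "linear mixed models will be used for continuous outcomes", and "generalized estimating equations will be used for categorical outcomes". It adds "Statistical significance will be considered at p < 0.05" and "The Holm procedure will be applied to address multiplicity". It does not name the clustering unit, working correlation, standard-error estimator or reference distribution for the GEE test.

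The article gives two cluster counts. Section 2.1: "Randomization will be carried out based on the 18 geographic districts in Hong Kong". Section 2.8: "We operationalize the 18 districts in Hong Kong into 4 clusters", a count used there to get an average cluster size of 260/4 = 65 and a design effect of 1.64.

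Section 2.10 fixes the layout. It begins with an all-control period, "All 18 districts will receive no interventions in the first 4 weeks", after which "4-6 districts will initiate the stepped-care CMH intervention and this procedure continues at 4-week intervals". With the four steps of section 2.1 this makes five 4-week periods.

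**The concern.** The ordinary GEE test divides the estimate by an empirical (sandwich) standard error and refers the ratio to a normal distribution. Both parts are justified when independent clusters are many. With few clusters the sandwich standard error is too small on average, and the normal distribution has thinner tails than the statistic. The test then rejects too often when the herbal intervention does nothing.

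What is at stake is the p-values and confidence intervals of outcomes analysed as categories. From section 2.6 these are mainly the type of professional consulted and, if analysed as categories, the 0-3 TCM symptom ratings. The Holm procedure does not help: it takes each p-value as valid and adjusts for their number only.

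**Working it through.** **The plan's own figure.** The only error rate in the article is the nominal 0.05, so the check is whether the ordinary test keeps to it.

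**Inputs from the article.** 18 districts (2.1) or 4 clusters (2.8); four steps of 4-6 districts at 4-week intervals after one control period (2.1, 2.10); ICC 0.01 (2.8); 428 participants after attrition and 612 recruited (2.8, taken as stated; how 260 was reached is a separate question).

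**Assumed inputs.** Event rates of 10% to 50%; ICC 0.05 as a second value; district splits of 4/5/5/4 (set A) and 4/4/5/5 (set B); how enrolment spreads over districts and periods; mostly one binary record per person.

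**Parameter count.** 5 period terms + 1 treatment term = 6. A sandwich covariance built from 4 clusters has rank at most 4 < 6, so with 4 clusters it cannot be of full rank. With 18 clusters, districts minus parameters = 18 - 6 = 12.

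**Effect of the reference alone.** If the statistic followed a t distribution, the chance of exceeding the normal cut-off of 1.96 would be 7.4% on 12 degrees of freedom and 6.8% on 16 (districts minus 2). Bias in the standard error adds to this.

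**Simulation with true treatment effect 0.** Logistic GEE with period and treatment terms, two-sided nominal 5%. Set A: 700-1,000 trials per scenario. Set B: 1,500 per cross-sectional scenario and 300-1,000 per cohort scenario, with independence and exchangeable working correlations.

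| Test | 18 clusters | 4 clusters |
|---|---|---|
| Uncorrected sandwich, normal (A) | 9.1-12.3% | 26.1-29.4% |
| Uncorrected sandwich, normal (B) | 8.1-10.1% | 28.0-38.9% |
| Uncorrected sandwich, t on clusters minus 2 (B) | 5.7-8.5% | 6.8-15.7% |
| Model-based, exchangeable, normal (B) | 2.9-7.3% | 10.5-17.3% |
| Bias-reduced sandwich, t on 12 df (A) | 2.7-5.1% | not given |
| Mancl-DeRouen, t on clusters minus 2 (B) | 3.1-5.5% | 0.7-2.3% |
| Kauermann-Carroll, t on clusters minus 2 (B) | 3.9-6.7% | 2.3-7.0% |

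Pooling A and B for the ordinary test:
- 18 clusters: 8.1/5 = 1.6 to 12.3/5 = 2.5 times nominal.
- 4 clusters: 26.1/5 = 5.2 to 38.9/5 = 7.8 times nominal.

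**Repeated measures.** Table 3 measures each participant several times. The cohort runs in set B (428 participants, ICC 0.01) gave 8.6%, 9.5% and 10.0% at 18 clusters, so the direction does not depend on one record per person.

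**Simulation error.** In set B the Monte Carlo standard error is √(0.09 × 0.91/1500) ≈ 0.007 near 9% and √(0.33 × 0.67/1500) ≈ 0.012 near 33%. For the 300-run cohort scenarios it reaches √(0.37 × 0.63/300) ≈ 0.028.

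**The case against.** The strongest reply is that section 2.15 does not state the test being criticised. It names GEE but no standard error or reference distribution, and it does not rule out a small-sample correction. Such detail commonly sits in a statistical analysis plan or full protocol, and neither is shown. GEE with 18 clusters is not in itself an error, and with a corrected standard error and a t reference it runs close to nominal. This stands: the inflation can only be stated conditionally.

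Three stronger readings are tempting, and the article does not support them.

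- A reader might infer that this trial's false-positive rate is several times nominal as a matter of plan. That needs the ordinary test, which the article does not specify. At 18 districts even that test gives 1.6 to 2.5 times.
- A reader might take the 26-39% as the expected rate because section 2.8 speaks of 4 clusters. That section uses the count only for the design effect. Sections 2.1 and 2.10 make the district the unit of randomisation and roll-out, and no section says the analysis clusters on 4.
- A reader might extend the point to the primary comparison. PHQ-9, GAD-7 and ISI are scale scores and go to the linear mixed model. The article defines no responder or remission endpoint.

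The reach is also small among secondary outcomes. SF-12, PSS-10, visit counts, expenditure and compliance are numeric. Table 3 schedules adverse events and compliance only immediately after treatment, with no scheduled control measurement to compare.

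The reply does not remove the point. The article commits to a method whose ordinary form suits few clusters badly, and it prints two different cluster counts, the quantity on which the validity of that method depends.

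**Conclusion.** The point holds as a conditional improvement for secondary categorical outcomes. If the GEE test is run with an uncorrected sandwich standard error and a normal reference, the false-positive rate with 18 districts is about 8-12% at a nominal 5%. The figure of about 26-39% belongs only to an analysis clustered on the 4 groups of section 2.8.

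The rates rest on a simplified design: assumed event rates, district split and enrolment by period, and mostly one record per person. The direction agreed in both sets of simulations and in the cohort runs; the exact percentages should not be read as predictions for this trial. This is worth correcting because it is cheap, but it does not threaten the main result.

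**What to change.** In section 2.15:

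1. State that the 18 randomised districts are the clusters in the GEE analysis, and reconcile this with the 4 clusters of section 2.8.
2. Specify a small-sample bias-corrected sandwich, for example Kauermann-Carroll or Mancl-DeRouen, with a t reference on cluster-based degrees of freedom. Either districts minus parameters (12) or districts minus 2 (16) is workable; choose one in advance. At 18 clusters the simulated rates under these choices were about 3-7%, with 12 degrees of freedom somewhat conservative in some scenarios.
3. Alternatively, specify a permutation test over the district sequence.

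The cost is one or two sentences and a different software option, with no new data or participants. Intervals for these outcomes become slightly wider and power slightly lower.
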